**Primary Outcomes – Patient-reported**						
PHQ-8 (depression)	x	x	x	x	x	x
GAD-7 (anxiety)	x	x	x	x	x	x
**Secondary Outcomes – Patient-reported and/or electronic health record**						
Resources used to prepare for surgery	x	x				
KOOS pain and ADL subscales	x	x	x	x	x	x
Lubben Social Network Scale	x	x	x	x	x	x
Short Form-12	x	x	x	x	x	x
Pain Catastrophizing Scale	x	x	x	x	x	x
General Self-Efficacy Scale	x	x	x	x	x	x
Opioid use	x	x	x	x	x	x
COVID-19 screener survey	x	x	x	x		
Exercise survey	x	x	x	x	x	x
Sleep disturbance (PROMIS)	x	x	x	x	x	x
Surgical outcomes			x	x	x	x
Program Evaluation			x	x	x	x
Knee range of motion	x	x	x	x		
Blood Pressure	x	x	x	x		
Resting Heart Rate	x	x	x	x		
Weight	x	x	x	x		
Timed up and go test	x	x	x	x		
6-min walk test	x	x	x	x		
30 second chair stand test	x	x	x	x		
Quadriceps Strength using a handheld dynamometer	x	x	x	x		

*EHR* Electronic health record, *PHQ – 8* Patient Health Questionnaire 8 items, *GAD-7* Generalized Anxiety Disorder 7 items, *KOOS ADL* Knee Injury and Osteoarthritis Outcome Score Activity of Daily Living Sub-scale, *COVID-19* Coronavirus disease 2019, *PROMIS* Patient-Reported Outcomes Measurement Information System

Other secondary outcomes include the post-surgery inpatient rehabilitation duration assessed by participant self-report at 6 months post-surgery, and change in the following objectively measured physical parameters from baseline to 6 months post-surgery: knee range of motion using a goniometer, Timed Up and Go test (TUG), 6 Minute Walk Test (6MWT), 30-Second Chair Stand test, and quadriceps strength using a handheld dynamometer (only for those that did the data collection in person) [62–64]. Table 5 contains information about the measures that will be collected in the study with the corresponding time points.

**Table 5 Tab5:** Detailed measures table

Name/Construct	Type (i.e., primary, secondary, other)	Time Frame	Description / Instrument
**Patient Health Questionnaire-8 (PHQ-8)** [55]	Primary	Baseline and 6-month follow up	The PHQ-8 is an 8-item scale that screens for depression. Scores range from 0 to 24 with higher scores indicating greater severity of depression
**Generalized Anxiety Disorder Assessment (GAD-7)** [54]	Primary	Baseline and 6-month follow up	The GAD-7 is a 7 item self-reported questionnaire for screening and severity measuring of generalized anxiety disorder. Scores range from 0 to 21, with higher scores indicating greater severity of anxiety
**Knee Injury and Osteoarthritis Outcome Score (KOOS) pain and function in daily living sub-scales** [59]	Secondary	Baseline and 6-month follow up	The KOOS pain sub-scale is a 9-item scale that assesses knee pain. Scores range from 0 to 100 with lower scores indicating greater severity of pain. The KOOS function sub-scale is a 17-item scale that assesses function. Scores range from 0 to 100 with lower scores indicating worse knee function
**Lubben Social Network Scale-18 (LSNS-18)** [56]	Secondary	Baseline and 6-month follow up	The LSNS-18 is an 18-item scale that measures perceived social support. Scores range from 0 to 90 with higher scores indicating greater social engagement
**12-Item Short Form Survey (SF-12)** [57]	Secondary	Baseline and 6-month follow up	The SF-12 is a 12-item scale that assesses general health status. Scores range from 0 to 100 with higher scores indicating better physical and mental health functioning
**Pain Catastrophizing Scale (PCS)** [58]	Secondary	Baseline and 6-month follow up	The PCS is a 13-item scale that assesses the level of catastrophic thinking related to an individual's pain. Scores range from 0 to 52 with higher scores indicating a higher level of pain-related anxiety
**General Self-Efficacy (GSE)** [60]	Secondary	Baseline and 6-month follow up	General self-efficacy (GSE) is a reliable and valid instrument to assess this disposition. This scale is a self-report measure of self-efficacy of 10 items. The total score ranges between 10 and 40, with a higher score indicating more self-efficacy
**Opioid use**	Secondary	Baseline and 6-month follow up	Self-reported use of opioids for knee pain
**Patient-Reported Outcomes Information System (PROMIS) Sleep Disturbance Scale** [61]	Secondary	Baseline and 6-month follow up	The PROMIS Sleep Disturbance Scale is a 8 item scale that measure self-reported perceptions of sleep quality, depth, and restoration within the past seven days. Scores range from with higher scores indicating greater sleep disturbances
**Surgical outcome**	Secondary	6-month follow up	Self-reported duration of inpatient rehabilitation
**Physical measurements**	Secondary	Baseline and 6-month follow up	Physical measurements will be collected by a blinded researcher in-person and from the electronic health record: Knee range of motion using a goniometer, blood pressure, resting heart rate, weight, time up and go test, 6-min walk test, 30 s chair to stand test, and quadriceps strength using a handheld dynamometer
**Program Evaluation**	Other	6-month follow up or after dropping out from the study	All participants will complete a program evaluation survey at the end of their time with the study or at the time they drop out
**Demographics**	Other	Baseline	Age, sex, race/ethnicity, education, insurance, income, work status, marital status
**Medical/Surgical history**	Other	Baseline	Diagnosed conditions, medications/treatments, previous joint replacement surgeries
**Social history**	Other	Baseline	Smoking, vaping, alcohol consumption history
**Implementation climate** [46]	Feasibility	6-month follow-up	We will determine the number of participants that completed the study in the attention control arm and Moving Well intervention arm and compare with how many initiate the study. The intervention will be considered feasible if more than 80% of enrolled participants complete the intervention and data collection points Retention of peer coaches in the study of 80% or more will be another metric that we will use for feasibility
**Implementation and Evaluation climate** [46]	Reach	Baseline	We will collect demographic and social data on all the participants that join the intervention. We will store the demographic and social information of individuals that drop out from the study. This information will provide us with an understanding of how the intervention is reaching a diverse group of people with rheumatoid arthritis
**Implementation and Evaluation climate** [46]	Adoption	At 6-month follow-up data collection or after dropping out from the study	We will collect demographic and social data among all participants. We will also be inviting both participants that completed the study and those that drop out, to participate in semi-structured interviews regarding their experience with the study, the Moving Well curriculum, and working with a peer coach. This information will allow us to improve the adoption of the intervention to a larger clinical trial
**Implementation and Evaluation climate** [46]	Implementation/ Fidelity	Calls of sessions 1–12 between peer coaches/research staff and participants	All calls between peer coaches and participants will be recorded and reviewed by the research team to assess fidelity of the intervention Peer coaches must have discussed at least 80% of the items in the checklist of each of the sessions to make sure that the intervention is been delivered as intended. We will do additional training for peer coaches who are completing less than 80% of the corresponding session checklist
**Implementation and Evaluation climate** [46]	Maintenance	Weekly throughout the study (weekly calls with peer coaches) and after 6-month follow up data collection	We will conduct semi-structured interviews to determine the best way to support participants and peer coaches, to maximize retention for the Moving Well program, and receive feedback for the intervention

### Implementation and program evaluation

We will use the RE-AIM implementation and program evaluation framework for this study. We will track the number of participants that complete the study in the peer coach intervention arm and control arm. The feasibility of the study will be assessed by examining the completion of the program (80% of enrolled participants complete the intervention), and satisfaction among participants and peer coaches. We will perform one-sample tests on program adherence and high satisfaction in the *Moving Well* arm by comparing these outcomes with an 80% benchmark.

Demographics of eligible individuals who chose not to participate will be compared to those who did choose to participate to estimate the magnitude of selection bias and to gain an understanding of how the intervention is reaching a diverse group of people with KOA scheduled for TKR. Other feasibility outcomes include the completion rate of the intervention, duration of the phone calls between coaches and clients, sustainability of peer coaches’ network, and retention of peer coaches.

We will invite participants that completed the study and those that drop out to participate in semi-structured interviews regarding their experience with the study. This information will allow us to adapt the intervention for use in in a larger clinical trial. All calls between peer coaches and clients will be recorded and reviewed by the research team to assess the fidelity of the intervention. Peer coaches must have discussed at least 80% of the items in the checklist of each of the sessions to make sure that the intervention is been delivered as intended. We will do additional training for peer coaches that are completing less than 80% of the corresponding session checklist. Table 5 details the implementation and evaluation procedures of the intervention.

### Data analysis

We will use descriptive statistics, t-tests, and Chi-square tests as appropriate to compare patients in each study arm. We will assess group differences between baseline and the week before TKR, 6 weeks after TKR, and 6-, 12-, and 24-months after TKR with parametric and nonparametric analyses including one-sample t-tests, Wilcoxon rank sum, and Chi-square tests or Fisher’s exact test of proportions, as appropriate. All tests will be two-sided (unless otherwise stated) and the overall type I error will be maintained at 5%.

We will use linear and generalized linear mixed effects regression models to analyze the repeated measures of all outcomes. Although a significant treatment*time interaction will conclude rejection of the hypothesis, in this pilot study we will focus on obtaining estimates of baseline adjusted treatment effects at the end of treatment as preliminary evidence of effectiveness to power a future trial. We will correct the inflation of the type I error due to multiple primary outcomes using Holm’s stepdown procedure. Due to the exploratory nature of the secondary outcomes, we will not adjust the type I error. Our mixed models provide valid inferences when data are missing at random. However, we will also test the plausibility of this assumption and repeat our analysis using pattern-mixture models [65].

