**Methods:**

This is an open-label pilot randomized clinical trial that will test the feasibility and effectiveness of the *Moving Well* intervention compared to an attention control group, *Staying Well*, to reduce symptoms of anxiety and depression in patients with KOA undergoing TKR. The *Moving Well* intervention is guided by Social Cognitive Theory. During this 12-week intervention, participants will receive 7 weekly calls before surgery and 5 weekly calls after surgery from a peer coach. During these calls, participants will be coached to use principles of cognitive behavioral therapy (CBT), stress reduction techniques, and will be assigned an online exercise program, and self-monitoring activities to complete on their own time throughout the program. *Staying Well* participants will receive weekly calls of similar duration from research staff to discuss a variety of health topics unrelated to TKR, CBT, or exercise. The primary outcome is the difference in levels of anxiety and/or depression between participants in the *Moving Well* and *Staying Well* groups 6 months after TKR.

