### Study population and sample size

The participants of the study will be people with KOA who are 50 years of age or older, have a TKR scheduled in 8 weeks or more, speak English, have access to a computer, the internet, and a working phone. We will exclude people who are unable to exercise (wheelchair-bound or bedbound), have a history of any joint replacement surgery, or have any rheumatic disease other than KOA.

The peer coaches of *Moving Well* will be people with KOA who had a TKR at least 12 months before they initiate their training as peer coaches of the intervention. This study will have 5 peer coaches.

The sample size estimation assumed four repeated measures, a range of intra-class correlations (0.05 to 0.20) for the repeated measures, and a Bonferroni-adjusted overall type I error of 5% (after controlling for two primary outcomes). We estimate a 20% attrition rate and will recruit 93 subjects, resulting in 37 participants in each arm of the study (total of *N* = 74 completers). The trial is designed to have at least 80% power to detect a standardized effect size of d = 0.5 or 0.5 standard deviations between the intervention and attention control arms. The standardized effect size is equivalent to a 2.7-point change in the PHQ-8 score, and a 1.6-point change in the GAD-7 score.

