### Primary and secondary outcomes

The primary outcome will be the difference in levels of anxiety and depression 6-, 12-, and 24-months post-surgery between *Moving Well* and *Staying Well*. The GAD-7 [54] and PHQ-8 [55] will be used to assess the participants’ level of anxiety and depression respectively. Participants will complete the data collection survey at baseline, 6-, 12-, and 24-months post-surgery. If participants have not completed the data collection surveys, a blinded member of the research team will follow up with a phone call to complete the forms over the phone and minimize missing data.

Secondary outcomes will include change from baseline to 6-, 12-, and 24-months post-surgery in the level of social support, general health status, level of pain catastrophizing, knee pain and function, level of self-efficacy, level of sleep disturbance, and opioid use for knee pain. Table 4 has details of the instruments that we will be using to measure primary and secondary outcomes and the time points that data collection will occur. These secondary outcomes will be measured respectively using the following: Lubben Social Network Scale-18 (LSNS-18) [56], 12-Item Short Form Survey (SF-12) [57], Pain Catastrophizing Scale (PCS) [58], Knee Injury and Osteoarthritis Outcome Score (KOOS) Pain and Activities of Daily Living (ADL) sub-scales [59], General Self-Efficacy Scale (GSF) [60], Patient-Reported Outcomes Information System (PROMIS) Sleep Disturbance Scale [61], and participant self-report use of opioids for knee pain.

**Table 4 Tab4:** Data collection timepoints and respective outcomes

	**Baseline**	**1-week pre- surgery**	**6-weeks post- surgery**	**6-months post-surgery**	**1-year post- surgery**	**2-years post-surgery**
Sociodemographic information (collected via EHR and patient survey)	x					
Medical history (collected via EHR and patient survey)	x					
Surgical history (collected via EHR and patient survey)	x					

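### The only test tied to rejecting the hypothesis is a treatment-by-time interaction, which matches neither the primary outcome (a between-arm difference in levels) nor the contrast that the sample size supports

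*Protocol article*

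**What the plan says.** Four places in the protocol article bear on which test decides the primary hypothesis.

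- **Data analysis.** Mixed models are fitted to the repeated measures, and "a significant treatment*time interaction will conclude rejection of the hypothesis". That clause is concessive. The main clause says "we will focus on obtaining estimates of baseline adjusted treatment effects at the end of treatment", as preliminary evidence to power a later trial. The section also holds the overall type I error at 5% and applies Holm's procedure to the primary outcomes.
- **Abstract, Methods.** "The primary outcome is the difference in levels of anxiety and/or depression between participants in the" two arms, at 6 months after surgery.
- **Primary and secondary outcomes.** "The primary outcome will be the difference in levels of anxiety and depression 6-, 12-, and 24-months post-surgery between" the two arms, on the GAD-7 and PHQ-8.
- **Study population and sample size.** The calculation "assumed four repeated measures, a range of intra-class correlations (0.05 to 0.20) for the repeated measures", with Bonferroni adjustment for two primary outcomes. "The trial is designed to have at least 80% power to detect a standardized effect size" of 0.5 between the arms, with 37 completers in each. No interaction is mentioned.

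**The concern.** A difference in levels asks whether the arms are apart after surgery. A treatment-by-time interaction asks whether the gap between the arms changes over time. The two coincide only in part, and how far depends on whether baseline is an outcome row or a covariate, which the article does not say.

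The stake is a misleading null result. If the intervention produced the planned 0.5 SD benefit and held it, the stated rule would usually not reject, and that could be reported as lack of effect although the trial was sized to detect such a benefit. The rule also ignores direction and does not identify the visit at which the arms differ.

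**Working it through.** **Inputs from the article.** 37 per arm; standardized effect 0.5 (SD = 1); ICC ρ = 0.05 to 0.20; four repeated measures; two-sided tests; 5% overall over two scales, so alpha = 0.025 each (also Holm's first step). The survey times given in the outcomes section are four ("Participants will complete the data collection survey at baseline, 6-, 12-, and 24-months post-surgery"); Table 4 lists six visits for both scales.

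**Assumptions added here.** Compound symmetry, no arm difference at baseline, and a constant 0.5 SD difference at every later visit.

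**1. Reproducing the plan's figure.** Recruitment: 74/0.8 = 92.5, so 93, as stated. For a between-arm difference averaged over m measures, SD = √[(1+(m−1)ρ)/m] and power ≈ Φ(0.5/(SD·√(2/37)) − 2.241), with √(2/37) = 0.2325.

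| m | ρ | SD | 0.5/SE | Power |
|---|---|---|---|---|
| 4 | 0.05 | 0.536 | 4.01 | 96% |
| 4 | 0.20 | 0.632 | 3.40 | 88% |
| 3 | 0.05 | 0.606 | 3.55 | 90% |
| 3 | 0.20 | 0.683 | 3.15 | 82% |

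So the stated power of at least 80% holds for this averaged contrast.

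**2. Interaction, baseline as an outcome row, categorical time.** The noncentrality is λ = (37/2)·SS/(1−ρ), where SS is the sum of squared deviations of the arm differences from their mean over visits.

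- Four visits: differences 0, 0.5, 0.5, 0.5, mean 0.375. SS = 0.375² + 3×0.125² = 0.1875. λ = 18.5×0.1875/0.95 = 3.65, or /0.80 = 4.34. On 3 df, power is 23.4% to 28.4%.
- Six visits: SS = 0.25×5/6 = 0.2083. λ = 4.06 to 4.82. On 5 df, power is 20.5% to 25.1% (20.1% to 24.6% with the noncentral F).

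**3. Other codings at alpha 0.025, ρ from 0.05 to 0.20.**

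| Coding | Power |
|---|---|
| One-df, mean of later visits minus baseline, four visits | 37% to 44% |
| The same, six visits | 41% to 48% |
| Linear in visit number, four visits | 22% to 26% |
| Linear in months, four visits | 17% to 21% |
| Linear in months, six visits (visit times assumed) | 9% to 10% |

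At Holm's second step (alpha 0.05) the figures are 33% to 39% on 3 df, 30% to 35% on 5 df, and 48% to 59% for the one-df contrast. At an assumed ICC of 0.60, well outside the plan's range, the omnibus test at alpha 0.025 reaches 59% (four visits) or 55% (six).

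**4. Baseline as covariate, follow-up visits only as outcomes.** A constant difference gives SS = 0, hence λ = 0, and power equals alpha: 2.5%.

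**5. Candidate replacements at alpha 0.025.**

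- Baseline-adjusted mean of the three follow-up visits: variance (1+2ρ)/3 − ρ² = 0.364 at ρ = 0.05 and 0.427 at ρ = 0.20. Power is 91% and 85%.
- Baseline-adjusted difference at one visit: SD = √(1−ρ²) = 0.999 and 0.980. Power is 46% and 48%.

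**The case against.** The strongest reply is that the interaction sits in a subordinate clause and the pilot's declared focus is estimation of baseline-adjusted effects. That stands and limits the damage. It does not remove the rule: Holm's procedure needs a p-value for each scale. Simple two-group tests are also listed in the section, but the interaction is the only test tied to rejection of the hypothesis.

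A second reply is that the Background states the hypothesis as lower levels relative to both baseline and control, which is differential change. The four survey times include baseline, so baseline as an outcome row is a natural reading. This also stands. A reader might infer that the interaction does not test the between-arm difference at all. That goes too far: under randomization, with baseline as an outcome row, it is a test of any follow-up difference, though a weak one. The 2.5% figure belongs only to the other model.

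Third, a reader might take 20% to 28% as following from the plan's inputs alone. It does not. It also needs categorical time, compound symmetry and a step-shaped effect, none of which the article states; hence the wider range above.

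Fourth, rejection when the 6-month difference is nil is not necessarily an error, because the outcomes section also places the primary outcome at 12 and 24 months. It would conflict only with the abstract's 6-month definition.

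**Conclusion.** The point holds as a mismatch between three stated elements: the rejection rule, the primary outcome and the powered contrast. It is something the article states, not a detail left to an unseen analysis plan. At the plan's ICC range and alpha 0.025, no coding examined gives the interaction more than about 48% power against a steady 0.5 SD benefit. The omnibus form gives 23% to 28% with four visits and about 20% to 25% with six, against 82% to 96% for the averaged between-arm effect.

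These figures rest on the assumptions listed in the working; an effect that grows or fades would give others. Because estimation is the declared focus, the documents do not support saying that the pilot as a whole would fail. They support saying that its formal test would usually miss the effect for which it was sized.

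**What to change.** Replace the rejection rule in Data analysis with a baseline-adjusted between-arm contrast from the same mixed model, for each scale, reported with its 95% confidence interval and tested at the Holm level. Report the interaction only as a description of how the effect changes over time.

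Then choose the contrast:

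- **Averaged over 6, 12 and 24 months.** This matches Primary and secondary outcomes and keeps the stated power (85% to 91%). Its cost is that it does not single out 6 months, so the Abstract must change.
- **At 6 months alone.** This matches the Abstract, but the power in Study population and sample size must be restated as about 46% to 48% at alpha 0.025, and Primary and secondary outcomes must change. A 6-month contrast does not by itself restore 80%.

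Either way, align the Abstract, the sample-size paragraph, the outcome definition and Data analysis on the chosen contrast. That includes the end-of-treatment wording, since the calls end five weeks after surgery. The change needs no new data and no new model family, but it touches several paragraphs, not one sentence.

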### Data management

All data will be collected using REDCap. Research staff will code all data fields to identify queries generated by REDCap and address them appropriately. Research staff will receive a unique login and password for the REDCap system and will be able to view and verify data accuracy. All participant data will be stored on secure HSS and WCM network servers.

